## Abstract

**Background:**

Kenya continues to experience persistent gender disparities in HIV testing. Young men remain substantially less likely than young women to test for HIV, despite expansion of facility based, community based, and HIV self testing services. Although WhatsApp based and peer led interventions have shown promise individually, it remains unclear whether adding online peer influencer engagement to standard HIV communication further increases HIV testing uptake.

**Objective:**

To determine whether adding an online peer influencer led WhatsApp intervention to standard FM radio and WhatsApp HIV messaging increases HIV testing uptake among young adult men aged 18–32 years in Nairobi, Kenya.

**Methods:**

A three-arm, age-stratified randomized controlled trial (1:1:1 allocation) will recruit young adult men aged 18–32 years online in Nairobi. Participants will receive either (i) FM radio HIV messaging, (ii) FM radio plus standard WhatsApp HIV messaging, or (iii) FM radio plus WhatsApp messaging with an online peer influencer intervention. Participants will be followed for 12 weeks. The primary outcome is verified HIV testing uptake, defined as completion of at least one HIV test during follow up and confirmed through participant self report, de-identified facility records, and a Unique Referral Identification Code (URIC). Primary analyses will use generalized linear mixed models under an intention-to-treat framework, with prespecified secondary analyses.

**Discussion:**

This trial addresses an important evidence gap by evaluating the added value of online peer influencers in increasing verified HIV testing uptake among young adult men in Nairobi, beyond standard radio and WhatsApp HIV messaging.

**Conclusion:**

Findings will provide rigorous evidence to inform HIV testing policies and scalable digital behavior change interventions targeting young men in Nairobi and similar urban settings.

**Clinical trial registration:**

https://pactr.samrc.ac.za/Researcher/ManageTrials_v2.aspx, Identifier PACTR202605857599507.

## Introduction

1

Despite substantial progress in Human immunodeficiency virus (HIV) prevention and treatment, Kenya continues to experience a high HIV burden, with approximately 1.4 million people living with HIV (PLHIV) (1, 2). Additionally, recent increases in HIV incidence and acquired immunodeficiency syndrome (AIDS) related mortality over the past 3 years are of public health concern (2). National surveillance data indicate a steady increase in new HIV infections, from 16,752 cases in 2023 to 19,991 in 2024 and 20,105 in 2025, with approximately 22,000 cases projected for 2026 (2). AIDS related deaths have followed a similar pattern, increasing from 18,473 in 2023 to 20,480 in 2024 and 21,009 in 2025, with approximately 23,000 deaths projected for 2026 (2). Although these trends are likely influenced by multiple factors including the coronavirus disease 2019 (COVID-19) pandemic and changes in funding for HIV/AIDS, among others. They highlight the need for renewed efforts to innovate more cost-efficient HIV testing strategies that maximize cost effectiveness by accelerating early diagnosis and uptake.

While overall national HIV testing uptake has improved, men remain significantly less likely than women to go for an HIV test and to know their HIV status (2). A key driver of Kenya’s increase in HIV incidence is low HIV testing rates. With fewer men than women going for an HIV test to screen for the virus (40). Multiple structural, behavioral, and health system factors contribute to low testing uptake among young men, including HIV related stigma, fear of positive results, concerns about confidentiality, perceived low risk, limited male friendly services, and competing socioeconomic priorities (2, 3). Conventional HIV testing promotion strategies, including facility based outreach and mass media campaigns such as radio, have had limited effectiveness in reaching this population (4). Consequently, internet based, social media interventions are proving effective particularly among young men (1, 5). Although HIV self testing (HIVST), launched in Kenya in (6) to address the stigma associated with facility based HIV testing for men, has expanded access to HIV testing among men, linkage to confirmatory testing and treatment remains suboptimal (2). Fewer than half of HIVST users are successfully linked to care (2, 7). Consequently, innovative interventions that both increase HIV testing and encourage linkage to health facilities remain necessary (1–5).

WhatsApp has emerged as one of the most widely used internet based communication platforms in Kenya, particularly among young adult males living in Nairobi (8–10). According to DataReportal (9) estimates, Kenya has approximately 27.4 million internet users and more than 68 million mobile connections, equivalent to 121% of the population. With about 75% of the Kenyan population under 35 years of age (11, 12), this accounts for what can be described as a youth led digital boom. Making WhatsApp a suitable platform for delivering digital health interventions in Kenya (43).

Nairobi County reports the highest absolute number of new HIV infections of any county in Kenya and has the largest number of HIV Testing Services (HTS) sites nationwide. Combined with high internet connectivity and widespread smartphone use among young adults; these characteristics make Nairobi an appropriate setting for evaluating an innovative social media based intervention to improve HIV testing uptake among young adult men (2, 7, 8).

Chory et al. (53), Ronen et al. (13) and Sheira et al. (14), have demonstrated that in Kenya WhatsApp based peer support interventions are highly acceptable, organically adopted and widely used for communication by young people living with HIV. These studies also demonstrate that WhatsApp can improve HIV related knowledge and behavioral outcomes among young men living with HIV in Kenya. Across sub Saharan Africa, recent studies show an up to 50% increase in HIV testing uptake among men when peer led interventions are used (15, 16). The Owete Trial shows the particular effectiveness of online peer driven interventions at increasing HIV testing uptake among Kenyan men (13). These studies demonstrate that WhatsApp based interventions, peer support programmes and digital health communication can improve young adults’ engagement with HIV services (41). However, it remains unclear whether adding online peer influencer engagement to standard HIV messaging provides additional benefit in increasing verified HIV testing uptake among young adult men in Nairobi, Kenya. This question forms the basis of this randomized controlled trial (RCT).

Although WhatsApp based interventions and peer led approaches have independently demonstrated effectiveness in improving HIV related outcomes, evidence evaluating the additional benefit of adding online peer influencer engagement to standard radio and social media based, HIV testing interventions for young men remains limited. This study addresses that important evidence gap by determining whether adding an online peer influencer component to standard FM radio and WhatsApp, HIV messaging, results in greater HIV testing uptake among young adult men in Nairobi.

## Methods

2

### Study design

2.1

This study is a three arm, parallel group, age stratified; randomized controlled trial (RCT) with equal allocation (1:1:1) will be conducted over a 12 week period. The trial compares the effectiveness of three different HIV testing uptake promotion strategies of increasing intensity: Arm 1 (active control), Arm 2 (comparator), or Arm 3 (intervention). Participants will be followed for 12 weeks, with outcome assessments at baseline (0) and weeks 2, 6, 10, and 12 using a repeated measures framework (17, 18, 56).

Consistent with the parallel group design framework established by Schulz et al. (18), the three different study arms (WhatsApp groups) will each concurrently receive different interventions promoting HIV testing uptake during the 12 week study period.

### Trial registration

2.2

The trial was registered with the Pan African Clinical Trials Registry (PACTR) (Trial ID: PACTR202605857599507) prior to participant recruitment to ensure transparency and reduce the risk of selective reporting. The protocol was developed in accordance with the Standard Protocol Items: Recommendations for Interventional Trials (SPIRIT) 2013 Statement (19). The completed trial will be reported in accordance with the Consolidated Standards of Reporting Trials (18, 60). Ethical approval was obtained from the Kenya Medical Research Institute (KEMRI) Scientific and Ethics Review Unit (SERU), and research authorization was granted by the National Commission for Science, Technology and Innovation (NACOSTI) before participant recruitment.

### Rationale for not conducting a pilot study

2.3

Operating without an independent pilot phase, the operational architecture of this RCT is directly modeled upon extensive research of highly similar trials demonstrating that both full digital interventions and online peer influencer frameworks effectively increase HIV testing uptake among young adult males in urban East Africa (15, 16).

### Study setting

2.4

This study will be conducted in Nairobi County, Kenya, using a hybrid online-to-facility design that integrates digital HIV testing demand generation with facility based HIV testing and linkage to care.

#### Geographic context

2.4.1

The study will be conducted in Nairobi, Kenya’s capital and largest urban centre. Nairobi has a large population of young adults, widespread smartphone ownership, high internet connectivity, and extensive use of social media platforms, particularly WhatsApp. Making it an appropriate setting for evaluating digitally delivered HIV testing interventions.

Nairobi consistently reports the highest absolute number of new HIV infections among Kenya’s counties and remains a priority area for HIV prevention and testing interventions (2). Although HIV prevention and testing services are widely available, gender disparities persist, with young men demonstrating lower HIV testing uptake and lower linkage to care than women, contributing to disproportionately higher AIDS related mortality rates among men (2).

Nairobi has an extensive network of Ministry of Health accredited HIV Testing Services (HTS) facilities and Comprehensive Care Clinics (CCCs), providing appropriate infrastructure for HIV testing, outcome verification, and linkage to care during the trial (51).

#### Digital context

2.4.2

Nairobi has high levels of internet connectivity, smartphone ownership, and social media use, particularly among young adults. WhatsApp is one of the most widely used messaging platforms in Kenya, providing a scalable and acceptable platform for peer driven health communication and digital intervention delivery (8).

#### Partner facility

2.4.3

The study will partner with a Ministry of Health-accredited Level 2 community health facility located in Kibra Sub-county, Nairobi. The facility provides 24-h outpatient services, HIV Testing Services (HTS), a Comprehensive Care Clinic (CCC), tuberculosis (TB) treatment, maternity services, and minor surgical procedures. The facility is registered on the Ministry of Health Master Facility List (MFL) and will serve as the primary site for HIV testing verification and linkage to care during the trial (20).

#### Hybrid online-to-facility model

2.4.4

The study employs a hybrid online-to-facility intervention model in which HIV testing demand is generated on WhatsApp, while HIV testing, verification, and linkage to care occur through the participating partner HTS facility (1, 21). This model seeks to address the persistent gap in linkage to care by encouraging participants to access confirmatory HIV testing and HIV care through the partner HTS facility (2, 7). Participants assigned to the intervention arm will be encouraged by trained online peer influencers to attend the partner HTS facility for HIV testing and linkage to care where appropriate.

The hybrid model combines:

*Digital delivery:* Recruitment, screening, informed consent, enrolment, randomization, intervention delivery, follow up, and participant engagement via WhatsApp*Facility based services:* HIV testing, confirmatory testing where required, referral code redemption, outcome verification, and linkage to care

### Study population

2.5

Young adult men were selected as the target population because they consistently demonstrate lower HIV testing uptake, delayed diagnosis, lower engagement across the HIV care cascade, and higher AIDS related mortality than women despite representing a smaller proportion of people living with HIV in Kenya (1, 2).

#### Target population

2.5.1

The target population comprises all young adult men aged 18–32 years residing in Nairobi County.

#### Study population

2.5.2

The study population comprises all eligible young adult men aged 18–32 years residing in Nairobi County who meet the eligibility criteria, provide informed consent, and are recruited through the study’s online recruitment strategy.

#### Sampling frame

2.5.3

The sampling frame consists of eligible members of the partner FM radio station’s Facebook community and affiliated digital platforms who voluntarily respond to the online recruitment campaign.

### Recruitment

2.6

Recruitment will be conducted entirely online. Study advertisements will be broadcast through the partner FM radio station and disseminated via its Facebook page and other approved digital platforms. Interested individuals will access an online eligibility screening questionnaire through a study specific Uniform Resource Locator (URL) or Quick Response (QR) code.

Eligible participants will complete electronic informed consent followed by the baseline questionnaire. Recruitment, screening, consent, enrolment, and follow up will all be conducted online. No face-to-face or community based recruitment will occur.

Recruitment channels include:

Partner FM radio broadcastsFacebook recruitmentDissemination through partner organizations and community networks

### Eligibility criteria

2.7

#### Inclusion criteria

2.7.1

Participants must:

Be maleBe aged 18–32 yearsReside in Nairobi CountyOwn or have regular access to a smartphone with WhatsAppprovide electronic informed consent

#### Exclusion criteria

2.7.2

Participants will be excluded if they:

Are currently receiving antiretroviral therapyAre participating in another HIV testing interventionLack access to WhatsAppAre unable or unwilling to provide informed consent

### Sample size determination

2.8

The primary outcome of this trial is HIV testing uptake, defined as completion of at least one HIV test during the study period. Because the primary outcome is binary and reported as a population proportion, the sample size was estimated using Cochran’s formula for proportions (22).

$$n0=(Z^{2}\cdot p\cdot q)/e^{2}$$

Where *Z* represents the critical value for a 95% confidence level (1.96), *e* denotes the acceptable margin of error (0.05), and p represents the estimated baseline proportion of HIV testing uptake. Given that the true HIV testing prevalence within this online male demographic was undetermined, *p* was conservatively set at 0.50 (*q* = 1 − *p* = 0.50) to assume maximum population variance and yield the most conservative sample size baseline. This primary calculation established a baseline requirement of 384 participants. To account for anticipated digital non-response and loss to follow-up, an approximate 22% attrition adjustment was applied (inflating the sample via *n* = *n*₀/0.82), resulting in a final cleared sample size of 468 participants allocated equally across the three study arms in a 1:1:1 ratio (156 participants per arm). Within each arm, participants will be stratified by age group prior to simple randomization to preserve developmental balance.

To validate this allocation against the primary objective, a supplementary power assessment was conducted using the standard formula for comparing two independent proportions:

$$n=[{\left(Z\_\{\alpha /2\}+Z\_\beta \right)}^{2}\cdot (p₁(1-p₁)+p₂(1-p₂))]/{\left(p₁-p₂\right)}^{2}$$

Where *α* is fixed at a two-sided significance level of 0.05 (*Z*_{*α*/2} = 1.96) and statistical power is fixed at 80% (*Z*_*β* = 0.84). Based on evidence highlighting depressed health seeking behaviors among young men in Kenya alongside historical peer led intervention data demonstrating up to 50% relative increases in testing uptake within sub-Saharan Africa, the calculation assumed an expected HIV testing uptake rate of 20% (*p*₁) in the active control arm and 40% (*p*₂) in the intervention arms (15, 16). This establishes an estimated absolute effect size of 20 percentage points.

Processing these assumptions confirms that an allocation of 156 participants per arm is statistically sufficient to detect absolute differences of approximately 20 percentage points between any single intervention arm and the active control group. While generalized linear mixed models (GLMMs) will be implemented for the longitudinal analysis of repeated outcome measurements, these serve purely as analytical frameworks rather than sample size estimation methods (17, 23). The trial is explicitly not powered to identify subtle variations within participant subgroups or to support definitive head-to-head hypothesis testing between the two intervention arms.

The study is powered to detect large intervention effects of approximately 20 percentage points in HIV testing uptake between study arms at a two-sided significance level of 0.05 and 80% statistical power. Subgroup analyses will be considered exploratory and interpreted cautiously (42).

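### The 20% v 40% planning effect is a doubling, but the evidence cited for it reaches at most a 50% relative increase (20% to 30%), for which the design has only about even odds

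*Protocol article*

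**What the plan says.** All of this is in section 2.8 of the protocol article (Sample size determination).

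- **Origin of N.** Cochran's formula for one proportion (Z = 1.96, p = 0.50, margin 0.05) gives 384. Division by 0.82 gives 468, or 156 in each of three arms.
- **Supplementary check.** A two-proportion formula is then printed, in which alpha "is fixed at a two-sided significance level of 0.05" and "statistical power is fixed at 80" per cent.
- **Effect.** Uptake is taken as 20% under active control and 40% in either intervention arm. Two grounds are named: low health seeking among young men, and "historical peer led intervention data demonstrating up to 50% relative increases in testing uptake within sub-Saharan Africa". From the two rates the section concludes: "This establishes an estimated absolute effect size of 20 percentage points".
- **Conclusions.** The section says that "an allocation of 156 participants per arm is statistically sufficient to detect absolute differences of approximately 20 percentage points" between an intervention arm and the control. It closes with: "The study is powered to detect large intervention effects of approximately 20 percentage points in HIV testing uptake between study arms", at two-sided 0.05 and 80% power.

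The Introduction cites the same two references for an increase of up to 50% and does not say whether this is relative or absolute.

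**The concern.** The effect size and the evidence offered for it stand in one sentence and do not agree. Evidence described as a relative increase of at most a half cannot support a doubling. The other evidence named there, low health seeking, can support a low control rate but not a 40% intervention rate. There was no pilot, and section 2.3 rests the design on the same two references.

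The power statement also does not describe the design. It pairs 156 per arm and 20 points with 80% power, although 156 was not obtained from a power calculation. A reader cannot learn from the section what difference this trial can detect with 80% power, or how it would perform at the effect its own evidence suggests. If an intervention arm achieved the full cited ceiling over radio alone, the trial would miss it about half the time, and nothing in the section warns of that.

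**Working it through.** **Inputs (all section 2.8).** Two-sided alpha 0.05 (1.96); power 80% (0.84); p1 = 0.20; p2 = 0.40; cited ceiling of a 50% relative increase; 384 before and 468 after attrition; 156 per arm.

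**1. The plan's own N.** 1.96² × 0.50 × 0.50 / 0.05² = 384.16. 384 / 0.82 = 468.3. 468 / 3 = 156. These figures reproduce. The formula gives ±5 points around one proportion in the pooled sample; it contains no comparison between arms.

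**2. The effect.** 0.40 / 0.20 = 2.0, a 100% relative increase. The cited ceiling gives 0.20 × 1.5 = 0.30, a difference of 10 points.

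**3. The printed two-proportion formula**, n = (1.96 + 0.84)² × [p1(1 − p1) + p2(1 − p2)] / (p1 − p2)²:

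- 20% v 40%: 7.84 × (0.16 + 0.24) / 0.04 = 78.4, so 79 per arm.
- 20% v 30%: 7.84 × (0.16 + 0.21) / 0.01 = 290.08, so 291 per arm evaluable, or 291 / 0.82 = 355 recruited.

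For 20% v 40%, other common choices give 82 (pooled variance), 91 (continuity-corrected), 109 (90% power), and 99 or 109 (Bonferroni for two or three comparisons). Inflating 79 to 91 for 18% or 22% loss gives 97 to 117. None is 156. The two-arm total 2 × 78.4 = 156.8 is close, but the section presents 156 as per arm and derives it as 468 / 3.

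**4. Power of the planned design.** Evaluable per arm after the 0.82 factor: 156 × 0.82 = 128. Unpooled normal approximation: power = Φ(|p1 − p2| / √{[p1(1 − p1) + p2(1 − p2)] / n} − 1.96).

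- 20% v 40%, n = 156: 0.20 / √(0.40/156) = 3.95; Φ(1.99) = 97.7%.
- 20% v 40%, n = 128: 0.20 / √(0.40/128) = 3.58; Φ(1.62) = 94.7%.
- 20% v 30%, n = 156: 0.10 / √(0.37/156) = 2.05; Φ(0.09) = 53.7%.
- 20% v 30%, n = 128: 0.10 / √(0.37/128) = 1.86; Φ(−0.10) = 46.0%.

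The table gives unpooled / pooled results. The detectable difference is found by solving each power formula for p2 at 80%.

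| Per arm | 20% v 40% | 20% v 30% | Difference from 20% detectable with 80% power |
|---|---|---|---|
| 156 | 97.7% / 97.4% | 53.7% / 53.2% | 13.9 / 14.0 points |
| 128 | 94.7% / 94.2% | 46.0% / 45.5% | 15.4 / 15.6 points |

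**5. Attrition range.** The section labels the adjustment about 22%, but a divisor of 0.82 is an 18% loss. If 22% were really lost, 156 × 0.78 = 122 per arm would remain. Power would then be 93-94% for 20% v 40% and about 44% for 20% v 30%.

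**The case against.** The section never says that the two-proportion formula yields 156. It calls that formula a supplementary check and concludes only that 156 is sufficient for about 20 points. Since 79 would do, that conclusion is true, and the 80% label understates power. It also ties the 80% to large effects and claims no power for 20% v 30%. All of this stands. A reader might infer that 156 is too few for 20 points, or that the article promises 80% power for a 10-point difference; the document supports neither reading.

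Three further inferences should be resisted:

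- **That p = 0.50 contradicts the 20% control rate.** The section sets 0.50 openly as a worst case for the variance, which can coexist with a 20% planning assumption. The fair criticism is that a precision formula does not address a comparison of arms.
- **That these figures show how a null result on peer influencers would be misread.** They concern an intervention arm against the radio control. The influencer increment is Arm 3 against Arm 2, and section 2.8 disclaims power for definitive testing between those two arms.
- **That the cited trials found a 50% relative increase.** The references are not at hand. The Introduction leaves the scale open, and if the increase were absolute, 20 points would lie within the ceiling. What can be shown is that section 2.8 disagrees with itself.

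None of this removes the mismatch between a stated ceiling of 50% relative and an assumed doubling.

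**Conclusion.** The concern holds in this form: the 40% assumption exceeds what the evidence is said to support, and the 80% power figure is not the power of this design at 20 points. The 80% errs on the conservative side, with actual power of about 97% at 156 per arm and 94-95% at 128. The effect size matters more: at the cited ceiling, power is about 53-54% at 156 and about 46% at 128. The difference detectable with 80% power is about 14 or 15-16 points, and the section does not state it.

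These figures assume a 20% control rate, a single two-sided 0.05 comparison of one intervention arm with the active control on the binary endpoint, normal approximations, and section 2.8's own description of the evidence as relative.

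**What to change.** Keep N = 468 and replace the power statement with wording such as:

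> With 156 per arm (128 evaluable after the 0.82 attrition factor), each comparison of an intervention arm with the active control has 80% power for a difference of about 14 (15-16) points from 20%, about 97% (94-95%) power for 20% v 40%, and about 53% (46%) for 20% v 30%, the upper limit of a 50% relative increase.

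Then:

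- Justify 40% from a source, or label it an assumption.
- Check the cited evidence and, if the word relative is the misstatement, correct it; the closing clause of the wording above would then change too.
- Keep the Cochran calculation as the stated origin of N, because 468 has no other derivation, but label it a precision calculation and not a power calculation.

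The cost is a text change, with no effect on recruitment, conduct or analysis. The downside is that the stated power for the effect the cited evidence supports becomes less favourable. Reaching 80% there would take about 355 recruited per arm (3 × 355 = 1,065 in total), which is not proposed here.

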### Outcome verification

2.16

PEach participant will receive a Unique Referral Identification Code (URIC) for enrolment. The URIC is a unique study generated identifier that anonymously links participant self reports with partner health facility records without recording personal identifiers in the research database.

Participants will present their URIC whenever attending the partner HTS facility for HIV testing. Facility staff will record the URIC together with confirmation that HIV testing was completed.

HIV testing uptake will be verified using three complementary data sources:

Participant self report;Anonymized partner facility HIV testing records; andURIC redemption.

A participant will be classified as having completed HIV testing only after facility verification confirms test completion. This hybrid verification model minimizes outcome misclassification, reduces recall bias, strengthens internal validity, and preserves participant confidentiality (29). This approach improves validity by reducing reliance on self report alone and is consistent with best practices in behavioral intervention trials (29).

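### Section 2.8 plans on 20% v 40% for any HIV test, but the outcome counts only partner-facility-verified tests; with equal capture across arms, 80% power needs about 60% to 73% of testers to be verified

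*Protocol article*

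**What the plan says.** All references are to the protocol article.

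- **Section 2.8, outcome.** For the sample size, testing uptake is "defined as completion of at least one HIV test during the study period". No facility or verification condition is attached.
- **Section 2.8, planning rates.** "the calculation assumed an expected HIV testing uptake rate of 20"% for Arm 1, against 40% for the other two arms. The support offered is evidence on young men's general health seeking and on uptake in peer-led programmes.
- **Section 2.8, power statement.** "The study is powered to detect large intervention effects of approximately 20 percentage points in HIV testing uptake between study arms". The power claimed is 80%, with a two-sided test at the 5% level.
- **Section 2.16, classification rule.** "A participant will be classified as having completed HIV testing only after facility verification confirms test completion". The Abstract likewise calls the primary outcome verified uptake.
- **Section 2.4.3, where verification happens.** The only facility described is one Level 2 facility in Kibra Sub-county, which "will serve as the primary site for HIV testing verification and linkage to care during the trial".
- **Sections 2.5.1 and 2.7.1, who is enrolled.** Men resident anywhere in Nairobi County. Section 2.4.1 adds that "Nairobi has an extensive network of Ministry of Health accredited HIV Testing Services (HTS) facilities".
- **Discussion.** It concedes that tests done outside participating facilities may be missed.

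The wording is not uniform. Section 2.15.1 repeats the any-test definition. Section 2.17.1 says the primary outcome is measured by questionnaire. Section 2.18 and the Discussion refer to facilities in the plural.

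**The concern.** A man who tests at another site in the county counts as tested under the definition in 2.8 and as untested under the rule in 2.16. If the planning rates are any-test rates, each measured rate is the planning rate multiplied by the share of testers whose test is verified. A common share shrinks both the control rate and the gap between arms, and 2.8 does not provide for this.

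At stake is how a null result would be read. If testing really doubled but much of it took place elsewhere, the verified gap could fall well short of 20 points. A non-significant comparison could then be taken as no benefit of the digital arms, in a trial that describes itself as adequately powered. The Discussion mentions missed tests as a limitation but does not connect them to power.

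**Working it through.** **Inputs from section 2.8.** p1 = 0.20 and p2 = 0.40; two-sided 0.05 (1.96); 80% power (0.84); 156 randomised per arm. For attrition, 2.8 states about 22% but divides by 0.82, which is 18%. Both are carried: 156 × 0.82 = 128 and 156 × 0.78 = 122 per arm.

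**Assumed input.** f is the share of testers whose test is verified at the partner facility, taken as equal in every arm. The documents give no value, so a range is shown.

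**Step 1: the plan's own figure.** The formula in 2.8 is n = (1.96 + 0.84)² × [p1(1 − p1) + p2(1 − p2)] / (p2 − p1)². At 20% v 40% this is 7.84 × (0.16 + 0.24) / 0.04 = 78.4, so 79 per arm. With 156 per arm, power is about 97%, and with 128 about 94% to 95%. The statement that 156 is sufficient is right for those rates.

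**Step 2: scale both rates by f.** With p1 = 0.2f and p2 = 0.4f:

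n = 7.84 × (0.6f − 0.2f²) / (0.04f²) = 117.6/f − 39.2.

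Solving for f gives f = 117.6 / (n + 39.2):

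- 156 per arm: 117.6 / 195.2 = 0.60
- 128 per arm: 117.6 / 167.2 = 0.70
- 122 per arm: 117.6 / 161.2 = 0.73

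A pooled-variance test gives slightly higher thresholds: 0.61, 0.72 and 0.74.

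**Step 3: power over the range** (normal approximation, unpooled variance).

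| f | Verified rates | n per arm for 80% | Power, 156 | Power, 128 |
|---|---|---|---|---|
| 1.0 | 20% v 40% | 79 | 98% | 95% |
| 0.7 | 14% v 28% | 129 | 87% | 80% |
| 0.6 | 12% v 24% | 157 | 80% | 72% |
| 0.5 | 10% v 20% | 196 | 70% | 62% |
| 0.3 | 6% v 12% | 353 | 46% | 39% |
| 0.25 | 5% v 10% | 432 | 39% | 33% |

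The lower rows only illustrate. Nothing in the documents says that capture would be that low.

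**Step 4: smallest detectable difference at 80% power** (same formula, solved for p2).

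| Verified control rate | 156 per arm | 128 per arm |
|---|---|---|
| 5% | 9.2 points | 10.4 points |
| 10% | 11.4 points | 12.8 points |
| 20% | 13.9 points | 15.4 points |

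**Step 5: a fixed 20-point gap in verified uptake.** The formula asks most at 40% v 60%: 7.84 × 0.48 / 0.04 = 94.1, so about 94 per arm. At 5% v 25% it asks 47. Both are below 122, so this claim survives at any control rate.

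**Step 6: unequal capture.** Sections 2.4.4 and 2.10 describe encouragement to attend the partner facility only for Arm 3. If 30% of testers are verified in Arm 1 and 40% in Arm 3, the rates are 6% v 16% and n = 7.84 × (0.0564 + 0.1344) / 0.01 = 149.6, so 150 per arm. With 156 analysed, 80% power is reached at capture well under 60%.

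**The case against.** A reader might infer that the stated 80% power holds only if 60% to 70% of all tests happen at the Kibra clinic. The documents do not support that unconditional reading, for four reasons.

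- **What 2.8 claims.** It claims power for an absolute gap of about 20 points, and Step 5 shows that this holds for verified uptake at any control rate. This stands. What weakens is the expectation that a doubling of testing would yield such a gap.
- **Equal capture.** The threshold needs the same verified share in both arms. That is most plausible for Arm 2 v Arm 1. For Arm 3 v Arm 1, Step 6 shows that less capture can suffice. This also stands. But power gained because one arm is steered to the verifying clinic partly reflects unequal ascertainment, which is a question of bias and does not rescue the planning rates.
- **Meaning of the rates.** Section 2.8 never says outright whether 20% and 40% are any-test or verified rates, and the cited sources are not at hand. The any-test reading rests on the definition that opens 2.8 and on the evidence offered there. The authors may have meant verified rates, in which case 2.8 should say so.
- **Loss to follow-up.** If only facility records count, a man with no redeemed code could be counted as untested and all 156 retained, so the 60% threshold would apply. If loss does apply, the two attrition figures in 2.8 give 70% or 73%.

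Every participant also receives a referral code, the clinic is open around the clock, and the plural references to facilities may mean wider capture than one site. These are reasons why f could be high, but they do not supply a value.

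**Conclusion.** The point holds in conditional form. The power check in 2.8 is attached to an outcome without a facility condition, while 2.16 classifies on verified tests only, and nothing in 2.8 bridges the two. If 20% and 40% are any-test rates and capture is equal across arms, 80% power needs about 60% capture with 156 per arm analysed, and about 70% to 73% if the planned 18% to 22% loss applies. The capture share itself is unknown, so the documents do not show that the trial is underpowered. They show that its stated power has not been established for a doubling of testing measured as verified uptake. For Arm 3 v Arm 1 the threshold shifts with unequal steering, and any gain in power there must be read as possible bias.

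**What to change.** 1. Reconcile the primary outcome across sections 2.8, 2.15.1, 2.16 and 2.17.1, so that one definition states whether a test must be verified and at which facility or facilities.
2. In 2.8, restate the planning rates as facility-verified uptake over 12 weeks, with the reasoning for any allowance for tests done elsewhere.
3. Replace the single power statement with power and smallest detectable difference over a range of verified control rates (for example 5%, 10% and 20%), stating the equal-capture assumption and the number analysed.
4. Report the verified share by arm from the self-report and referral-code data already being collected. The four-week recall question at week 2 reaches back before randomisation, so such tests need to be separated out.

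This needs no change in sample size and no new data collection. The cost is rewording and a less favourable power statement.
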